**Design**

Implementation of multicenter phase II studies to assess safety, tolerability and efficacy of a combined regimen of oral valproic acid and carnitine will proceed in two parallel studies involving differing SMA cohorts. Preliminary safety data from a pilot clinical trial at the University of Utah site demonstrates that giving valproic acid without carnitine (C) supplementation is likely to deplete carnitine, potentially increasing toxicity and resulting in reduced strength and function, thus confounding results of a clinical therapeutic trial. Cohort 1 trial design is double-blind randomized intention to treat protocol for SMA “sitters”; parallel trial in Cohort 2 SMA “standers and walkers” to explore responsiveness of efficacy outcomes. Cohort 1 will involve SMA subjects with SMA 2 or nonambulatory SMA 3 “sitters”, 2 – 8 years of age. Cohort 2 will involve SMA 2 and 3 subjects: “standers and walkers”, 3 – 17 yrs of age.

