**Statistical Analysis, Data Analysis and Interpretation**

*Sample Size*

In the Pilot Natural History Study conducted in the GCRC at the University of Utah, we found that SMA Type 2 patients did not significantly change over a six-month period when measured with the Modified Hammersmith Functional Motor Scale-SMA (MHFMA-SMA). The standard deviation for this longitudinal group was 3.19. The two treatment groups differ over the first six months, thus the primary outcome will be change in Modified Hammersmith Functional Motor Scale-SMA from the second baseline to six months. A clinically meaningful change is taken to be a 3-point change. A sample size of 25 patients completing both the baseline and six-month evaluations will provide 90% statistical power with an effect size of 0.941, Type I error of 0.05 (two-sided). Assuming 20% attrition, then 60 total patients will be required.

The patients that can stand or walk will be evaluated in a cohort 2 arm. The primary endpoint will be the SMA-3 scales. When the sample size is 25, a two-sided 95.0% confidence interval for a single mean will extend 39% of the standard deviation from the observed mean; the confidence interval is based on the large sample z statistic. In order to ensure that 25 patients complete the therapy then 30 patients will be accrued.

*Statistical Analyses*

The primary aim is to compare change over the first six months on the MHFMA-SMA for the VPA+C arm versus placebo. The assumption of normality of the change scores will be checked, if it holds then a t-test will be performed comparing the difference in average change scores. Gender and age may affect MHFMA-SMA scores; as such a linear regression analysis that includes gender and age will be included along with treatment. This will be a confirmatory analysis. Subjects that drop out prior to six months will be excluded from the primary analysis. If the subjects had a 3-month evaluation then an additional analysis will be performed using the last observation carried forward approach to determine the effect on the outcome of subjects with missing data.

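### Cohort 1 is called intention to treat, but its primary test leaves out everyone who drops out before six months, so arm-related dropout could bias the comparison

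*Protocol*

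**What the plan says.** In the protocol's Design section: "Cohort 1 trial design is double-blind randomized intention to treat protocol". Under Statistical Analysis, Data Analysis and Interpretation, the endpoint is fixed: "the primary outcome will be change in Modified Hammersmith Functional Motor Scale-SMA from the second baseline to six months". The test follows, subject to a normality check: "if it holds then a t-test will be performed comparing the difference in average change scores". The analysis set comes next: "Subjects that drop out prior to six months will be excluded from the primary analysis".

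Two other analyses touch on missing data:

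- A supplementary carry-forward run: "If the subjects had a 3-month evaluation then an additional analysis will be performed using the last observation carried forward approach".
- Among the secondary analyses, generalised estimating equations (GEE) fitted to all measurements from the second baseline to month 12.

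The Sample Size paragraph plans for 20% attrition among 60 patients. Study procedures schedules functional testing at months 3 and 6, and moves the placebo arm to active treatment after month 6. The exclusion sentence is repeated for Cohort 2, which is a single treated group.

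**The concern.** An analysis that removes randomised children because of something that happens after randomisation is not intention to treat. The two statements are both current text, and nothing else in the protocol reconciles them. Because the protocol itself fixes the exclusion, this is not a detail left to a statistical analysis plan.

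Randomisation makes the two arms comparable at entry. A completer comparison keeps that property only if leaving is unrelated to outcome, or is related to it in the same way and to the same degree in both arms. There is reason to doubt this here. In the first six months only one arm takes valproic acid, with its dose raised towards a target trough level. The protocol's own rationale is that valproic acid without carnitine may deplete carnitine and so reduce strength and function. Carnitine is given to counter this, but the protocol does not claim that the risk is abolished. Dropout in one arm that is linked to motor function is therefore plausible, and the sole primary comparison would carry the resulting bias.

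**Working it through.** **Inputs from the protocol (Sample Size).** "The standard deviation for this longitudinal group was 3.19"; "A clinically meaningful change is taken to be a 3-point change"; and the plan "will provide 90% statistical power with an effect size of 0.941, Type I error of 0.05 (two-sided", with 25 completers, 20% attrition and 60 patients in total (30 per arm in Study procedures).

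**The plan's own figure.** 3 / 3.19 = 0.940, against the stated 0.941. With 25 completers per arm, the noncentral t distribution gives 90.3% power, so the stated 90% reproduces if 25 is read as per arm.

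**Children left out.** 0.20 × 60 = 12, leaving 48, or 24 per arm, with power of 89.1%. Power is hardly touched; the issue is bias.

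**Bias as an identity.** In one arm, completer mean − full-arm mean = dropout share × (completer mean − dropout mean). If 20% of the active arm leave, their change averages 1 to 3 points worse than that of completers, and placebo dropout is random, the bias is 0.2 × 1 = 0.2 to 0.2 × 3 = 0.6 points. That is 7% to 20% of the 3-point target.

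**Bias with dropout in both arms.** Assumptions not in the protocol: no true effect; normally distributed change with SD 3.19; 30 per arm; each child drops out when a latent normal variable, correlated ρ with poorer six-month change, exceeds a cut-off set by the dropout share p. The completer mean is then shifted upwards by

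ρ × 3.19 × h(p), where h(p) = φ(z) / (1 − p) and z is the upper-p normal quantile.

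The bias is ρ × 3.19 × [h(active) − h(placebo)], with h(0.10) = 0.195, h(0.15) = 0.274, h(0.20) = 0.350, h(0.25) = 0.424 and h(0.30) = 0.497. For 30% versus 10% and ρ = 0.5, this is 0.5 × 3.19 × (0.497 − 0.195) = 0.48 points. The type I error comes from simulating the completer t-test.

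| Dropout, active vs placebo | Bias in points at ρ = 0.3 / 0.5 / 0.8 | Two-sided type I error |
| --- | --- | --- |
| 20% vs 20%, same mechanism | 0 / 0 / 0 | about 5% throughout |
| 25% vs 15% | 0.14 / 0.24 / 0.38 | about 5% / 6% / 7% |
| 30% vs 10% | 0.29 / 0.48 / 0.77 | about 6% / 8% / 15% |

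Swapping the arms reverses the sign.

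**Equal rates alone are not enough.** If 20% leave each arm but leaving is informative only in the active arm, the bias is ρ × 3.19 × 0.350 = 0.33, 0.56 and 0.89 points.

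**Do the planned extra analyses repair this?**

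- *Carry-forward.* It is additional, so it does not replace the primary test. A child lost before month 3 is in neither analysis. For the others it assumes no change from month 3 to month 6.
- *GEE.* It does use dropouts' month-3 scores. But it is secondary, and it runs across the switch of the placebo arm to active drug, so its stated question is a sustained effect and not the six-month contrast.

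**The case against.** The strongest case against runs as follows.

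*The bias is conditional.* The protocol gives one attrition figure and no split by arm. At 25% versus 15% with modest correlation, the error rate stays close to nominal. Placebo families might leave for lack of benefit, which could bias against the active arm. This stands. A reader might infer that the randomised comparison is lost outright, or that the trial is tilted towards the drug. The documents support neither: the protocol opens the door to bias but fixes neither its size nor its direction.

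*The protocol already looks at missing data.* It does, and the longitudinal analysis means that carry-forward is not the only use of dropouts' month-3 scores. Neither analysis is the primary test, however, and neither addresses children lost before month 3.

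*A repeated-measures model is not a cure.* Correct. The scenarios above make dropout depend on the unseen six-month value, whereas such a model assumes missing at random. In a large-sample check of 30% versus 10% at ρ = 0.5, with half of the dropouts having month-3 data, the bias of 0.48 points falls only to about 0.42 (month 3 to month 6 correlation 0.5) or 0.34 (correlation 0.7). The fix therefore cannot rest on the model alone.

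*Dropping out is not the same as stopping drug.* A reader might infer that a child who stops drug but attends month 6 is excluded. The protocol does not say so; it leaves the term undefined.

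*Cohort 2.* A reader might extend the argument to the repeated sentence there. That group has no randomised comparison and is not labelled intention to treat. The exclusion may shift its mean change, but it breaks no randomisation.

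**Conclusion.** The point holds for Cohort 1. The Design and Statistical Analyses sections contradict each other, and as written the primary test is a completer analysis that could omit about 12 of 60 randomised children.

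The consequence is conditional: none if dropout is equal and arises in the same way in both arms, small under mild imbalance, and material under marked imbalance. Against the 3-point target, the tabulated biases run from 5% (0.14 / 3) to 26% (0.77 / 3). They assume normal change scores, the protocol's SD of 3.19, and dropout splits and correlations chosen for illustration. The contradiction itself rests on no assumption. It deserves correction before the data are collected, because month-6 scores not obtained after dropout cannot be recovered later.

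**What to change.** For Cohort 1:

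1. Reconcile the two sections by defining the primary analysis as all randomised children, analysed as randomised.
2. Define dropout separately from stopping study drug. State that children who stop drug are still asked to attend the scheduled month-6 motor assessment, and that those scores enter the primary analysis.
3. Include available month-3 scores through a likelihood-based repeated-measures model, with the month-6 treatment contrast as the test, and state that it is valid under missing at random.
4. Replace carry-forward with a delta-adjusted (tipping-point) sensitivity analysis that covers all children without a month-6 score, including those lost before month 3.
5. Keep the completer t-test as a sensitivity analysis.

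Items 2 and 4 are the core, because they address dropout that depends on unseen outcomes; the model in item 3 does not do so alone.

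The cost is rewording and somewhat more analysis work. No extra patients or scheduled visits are needed, since motor testing at months 3 and 6 is already planned. The one burden is that families who stop drug are asked to return for a visit already in the schedule.

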
Blood samples will be obtained either immediately before or after the nerve conduction testing. If the patient is going to be sedated, the blood draw will be done while the patient is still under sedation. Three to six milliliters of blood is needed at each visit to check for safety monitoring and drug levels. If patients elect to have their DNA collected for genetic studies, an additional five to ten milliliters will be collected during the course of the study. If a DEXA scan is to be completed during this visit, it will occur either immediately before or immediately after the MUNE procedure. The total time of testing on the first day, including all of the testing above, is approximately 2 hours.

Prior to the patient’s arrival for each study visit they will be given a 3 day dietary/supplement record, which they will asked to complete and bring with them. This information will be reviewed with them by a dietician either on their arrival or on the first day of testing. If patients forget to bring their completed dietary record, they will be asked to complete it the following week and return it promptly. The site coordinator will administer the parent questionnaire of the quality of life tool (PedQLTM), which must be filled out by the same parent at each visit. Total time to complete the questionnaires is about 15 minutes.

Clinical testing on the second day includes the following: A physical therapist will perform a functional assessment using either the Modified Hammersmith Functional Motor Scale – SMA (cohort 1) and the Project Cure Functional Motor Scale for SMA (cohort 2). Functional testing will last between 15 to 30 minutes. Patients 5 years of age or older will receive pulmonary function testing and myometry testing. A physical therapist will perform myometry testing which uses a small device to help measure strength of patients’ hand grip and arm flexion and leg extension. A technician will perform pulmonary function testing which includes routine spiromerty, maximum inspiratory pressure (MIP) and maximum expiratory pressure (MEP). This testing will take approximately 30 minutes. Patients 5 years or older will complete the age appropriate questionnaire of the quality of life tool PedQLTM on this day.

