Secondary endpoints include an evaluation of the change in MHFMA-SMA at 12 months. We will evaluate the change from second baseline to 12 months and compare both groups. This will be done using a t-test. Since all patients will cross over to VPA+C at six months, this evaluation will be exploratory to determine whether or not additional treatment time of 12 vs 6 months leads to additional functional benefit in the treatment cohort compared to the placebo cohort and compared to their baseline values. We will also look at the change in MHFMA-SMA from 6 to 12 months for both groups. In addition, generalized estimating equations will be used to incorporate all longitudinal measurements from the second baseline through 12 months to determine if there is a sustainable treatment effect. Additional secondary endpoints include: Pulmonary Function Testing in subjects over five years of age, quantitative SMN mRNA, Peds QL™, CMAP amplitude/area, and MUNE. These endpoints will be exploratory in nature. Some will be hypothesis generating, while others will be confirmatory for the MHFMA-SMA results.

*The analyses of the cohort arm will be as follows:*

The assumption of normality of the change scores will be checked, if it holds then a large-sample z-statistic confidence interval around the mean will be constructed. Change from baseline will be examined and reported with 95% confidence intervals. Gender and age may affect scores; as such a linear regression analysis that includes gender and age will be performed to determine their influence. Subjects that drop out prior to six months will be excluded from the primary analysis. If the subjects had a 3-month evaluation then an additional analysis will be performed using the last observation carried forward approach to determine the effect on the outcome of subjects with missing data.

Additional secondary endpoints include: Pulmonary Function Testing in subjects over five years of age, Quantitative assessment of SMN mRNA, Peds QL™, Maximum CMAP amplitude/area: ulnar nerve /hypothenar eminence, Ulnar MUNE, growth and vital sign parameters, dietary assessment. These endpoints will be examined at each time point with means and confidence intervals as well as an analysis over time. These exploratory analyses will aid in the design of follow-up studies in this cohort of patients.

*Randomization*

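### Cohort 2's 95% interval uses z with an estimated SD at n = 25 and so covers about 93.8%; its primary endpoint also lacks one agreed instrument, baseline and time point

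*Protocol*

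**What the plan says.** The Sample Size section plans Cohort 2 on precision. With 25 completers, "a two-sided 95.0% confidence interval for a single mean will extend 39% of the standard deviation from the observed mean", and it adds that "the confidence interval is based on the large sample z statistic". Thirty children are to be accrued so that 25 complete therapy.

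The Statistical Analyses section carries this choice into the analysis. Normality of the change scores is checked and, if it holds, "a large-sample z-statistic confidence interval around the mean will be constructed". Change from baseline is then reported with 95% intervals.

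On the endpoint, the Sample Size section says "The primary endpoint will be the SMA-3 scales". The Study procedures section names the functional assessment for this cohort as "the Project Cure Functional Motor Scale for SMA (cohort 2". The Background lists the Project Cure scale among the outcome measures and does not mention SMA-3 scales. The visit schedule says only that functional testing is done.

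**The concern.** There are two separate weaknesses in the same primary analysis.

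First, a z interval is exact for normal data only when the SD is known. The only SD in the protocol, 3.19, comes from the pilot natural history study of type 2 patients on the Modified Hammersmith scale. That is a different scale from the one given to Cohort 2, whose members may have type 2 or type 3 disease. The Cohort 2 SD will therefore be estimated from the sample, and an interval built with 1.96 is too narrow for its 95% label. The choice is harder to defend because z is applied exactly when normality is judged to hold, which is the case where t is exact. Cohort 1, with the same planned 25 per group and the same normality check, gets a t-test.

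Second, a reader cannot tell from the protocol exactly what the Cohort 2 primary result is. The label does not match the instrument in the procedures, and the text points to two different time points. In an open single-arm cohort, the primary measure should be fixed before data are seen.

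**Working it through.** **Inputs.** n = 25 completers, two-sided 95% and a stated half-width of 39% of the SD by z (Sample Size); z carried into the analysis if normality holds (Statistical Analyses); no Cohort 2 SD anywhere, so results are in SD units.

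**Step 1: reproduce the plan's figure.** Half-width by z = 1.960/√25 = 1.960/5 = 0.392 SD. The stated 39% is correct arithmetic for z.

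**Step 2: actual coverage of that interval.** The interval mean ± 1.96·s/√n covers the true mean when |mean − μ|/(s/√n) ≤ 1.96. For normal data this ratio follows t with n − 1 degrees of freedom, so coverage = 2·T(1.96; n − 1) − 1, where T is the t distribution function. At n = 25 this is 0.9383. A simulation of 400,000 samples of 25 gave 0.9387. Non-coverage is 6.2% instead of 5%, a loss of about 1.2 points.

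**Step 3: the t interval.** Half-width by t = t(0.975; 24)/√25 = 2.064/5 = 0.413 SD. This is 2.064/1.960 = 1.053 times the z width, or 5.3% wider, with exact 95% coverage under normality.

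**Step 4: sensitivity to the number analysed.**

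| n | z half-width (SD) | t half-width (SD) | coverage of z interval |
|---|---|---|---|
| 20 | 0.438 | 0.468 | 93.5% |
| 24 | 0.400 | 0.422 | 93.8% |
| 25 | 0.392 | 0.413 | 93.8% |
| 30 | 0.358 | 0.373 | 94.0% |

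The plan's own figures for Cohort 2 are 25 completers from 30, a loss of 5/30 = 16.7%. The n = 24 row assumes that Cohort 1's 20% attrition applies (30 × 0.8 = 24), which the protocol does not state for Cohort 2. The n = 20 and n = 30 rows only show the range. Keeping a half-width of 0.392 SD with t would take 28 completers (0.388 SD; 27 gives 0.396 SD).

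**Step 5: the endpoint statements side by side.**
- *Instrument.* Sample Size names the SMA-3 scales, in the plural and without definition. Study procedures names one functional motor scale, the Project Cure scale. The Cohort 2 analysis text names no scale, only change scores.
- *Baseline.* There are two baseline visits. The second is specified as the reference for Cohort 1; for Cohort 2 the text says only change from baseline.
- *Time point.* The Cohort 2 dropout rule leaves out of the primary analysis children lost before six months, which suggests month 6. Study procedures treats Cohort 2 for twelve months and Sample Size counts patients who complete therapy, which suggests month 12.

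**The case against.** The strongest reply is that the z/t difference hardly matters. It is 1.2 points of coverage and 0.021 SD of half-width (0.413 − 0.392), in an uncontrolled cohort that the Design section sets up to explore how responsive the outcomes are. The 39% is openly labelled as a z figure, and no sample size or conclusion is shown to change. This stands as to size. It does not make z the right choice, since t is exact in the very case where the plan uses z.

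A reader might go further and infer that the interval produces too many false claims of effect. The protocol sets no test, threshold or decision rule for Cohort 2, so that reading has nothing to attach to. The supported statement is that the reported precision is slightly overstated.

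On the endpoint, a reader might infer that the primary measure is never administered, or that the sponsor is free to pick an instrument afterwards. The documents support neither. Functional testing is scheduled at every study visit, Cohort 2 is assigned a single functional motor scale, and SMA-3 scales may be another name for it. Pulmonary function, SMN mRNA, quality of life, CMAP and MUNE are listed as secondary, so there is little room to choose an instrument. The time point leaves more room.

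It is also tempting to read second baseline to month 6 as the intended comparison. The six-month dropout sentence repeats the wording used for Cohort 1, where month 6 is primary because the randomised arms differ only until then. That reason does not apply to a single-arm cohort, so the sentence does not settle the matter.

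**Conclusion.** The point holds in a limited form. As written, the Cohort 2 interval labelled 95% covers about 93.8% at n = 25, and the planned half-width should be 41.3% of the SD rather than 39.2%. This rests on normal change scores, which is the plan's own condition for using the interval, and on an SD estimated from the sample, which follows because none is given. The loss is minor for an exploratory single-arm cohort, but it is a plain error with an easy remedy.

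The endpoint label is undefined and does not match the procedures, and the baseline and time point are not fixed consistently. This is a fault of specification. It does not show that the outcome goes unmeasured, and the documents do not establish which time point was meant. A statistical analysis plan was not available. Even if it defines the endpoint, the protocol sections still need to agree with one another.

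**What to change.** 1. In the Sample Size and Statistical Analyses text for Cohort 2, replace the large-sample z interval with the t interval (24 degrees of freedom at n = 25), and state the planned precision as 41% of the SD instead of 39%.
2. Reconcile the Study procedures, Sample Size and Statistical Analyses sections on the Cohort 2 primary endpoint, and name one instrument, one baseline and one time point. If SMA-3 scales means the Project Cure Functional Motor Scale, say so and use one name throughout. The choice of time point is for the sponsor, and the dropout rule and the definition of a completer should then match it.

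The first change is wording only. It needs no extra patients or visits if 41% is accepted as the planned precision; holding the half-width at 39% of the SD would need 28 completers instead of 25. The second requires a decision by the sponsor but no new assessments, since functional testing is already scheduled at both baselines and at months 3, 6 and 12.
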